### Ethical Considerations

This study received ethical approval from the Ministry of Defence Research Ethics Committee (1042/MODREC/20) in September 2020. Participants will be provided with an information sheet at least 24 hours before consenting to participation and given a verbal description of the study. Written informed consent will be obtained at the start of the first testing session. Adverse events and reactions will be reported to the trial committee and considered by a minimum of 3 trial committee members.

All data will be handled in accordance with the project’s data management plan and in compliance with the General Data Protection Regulation. All raw data will be pseudonymized during the trial. Anonymized data will be uploaded to the active research data storage system at Nottingham Trent University for a minimum of 10 years following the completion of the study. Data access rights will be provided only to the relevant members of the research team.

### Measurements

#### Menstrual Cycle Tracking

Menstrual cycle phase and length will be monitored in the EUM group; many participants may already be using a menstrual tracking app, which will aid in cycle prediction using historical cycle length data.

Participants will be asked to report day 1 of menses, and all subsequent laboratory visits will be planned according to their reported cycle length. To verify the predicted phases of the menstrual cycle, the EUM group will be given urine dip stick tests (LH surge test) to test for ovulation between days 10 and 15 of the menstrual cycle for a 28-day cycle to ensure that testing occurs during the ovulatory phase. Women will be scheduled for testing at their *predicted* ovulation but will be *actually* tested once they also produce a positive LH test; we expect these dates to coincide. If a woman does not ovulate during the testing cycle, she will be invited to retest the following month.

#### Venous Blood and Urine Sampling

Venous blood samples will be taken in a resting state after an overnight fast. For the EUM group, blood will be drawn at 4 time points: menses (days 1-3), midfollicular phase (day 7, for women with a 28-day cycle), ovulation phase (day 14 for women with a 28-day cycle), and midluteal phase (day 21 for women with a 28-day cycle). For COCP users, samples will be obtained on day 21 of the pill cycle and the final day of the pill-free week (day 28). LARC users will be tested at a single time point. First-void urine samples will be taken at the same time points as venous blood samples.

#### Biochemical Analyses

Analysis of biochemical markers of reproductive status, bone resorption and formation, and iron status (Table 1) will be performed at the Bioanalytical Facility, University of East Anglia (Norwich, United Kingdom), according to manufacturers’ instructions and under Good Clinical and Laboratory Practice conditions. Metabolites will be analyzed using the COBAS automated platform (Roche Diagnostics) for 17β-estradiol (pmol/L), follicle-stimulating hormone (U/L), LH (U/L), procollagen type 1 N-terminal propeptide (g/L), phosphate (mmol/L), intact parathyroid hormone (pmol/L), beta carboxy-terminal cross-linking telopeptide of type 1 collagen (g/L), osteocalcin (g/L), albumin-adjusted calcium (mmol/L), IGF-I (ng/mL), prolactin (ng/mL), free thyroxine (pmol/L), thyroid-stimulating hormone (mIU/L), ferritin (g/L), soluble transferrin receptor (nmol/L), and IGF binding protein 3 (ng/mL). Liquid chromatography tandem mass spectrometry will be used for measurement of serum testosterone (nmol/L); androstenedione (nmol/L); dehydroepiandrosterone sulfate (nmol/L); cortisol (nmol/L); progesterone (nmol/L); 25(OH)D3/D2; 24,25-dihydroxyvitamin D3/D2 (nmol/L) [29]; 1,25-dihydroxyvitamin D3/D2 (pmol/L); and hepcidin-25 (ng/mL). Plate-based enzyme-linked immunosorbent assay will be used to analyze bone-specific alkaline phosphatase (U/L; MicroVue, Quidel Corp.), relaxin (pg/mL), and IGF-binding protein 1 (R&D Systems, Inc.; pg/mL). All assays will be performed with an inter- or intra-assay precision coefficient of variation (CV) of <10% across their respective assay ranges. The performance of 25(OH)D and 1,25-dihydroxyvitamin D assays is certified by the vitamin D external quality assessment scheme [30].

Hemoglobin and ionized calcium will be measured by a portable blood analyzer (iStat Alinity). Bone calcium balance will be measured in first-void urine samples, determined from the ratio of naturally occurring stable calcium isotopes (^44^Ca:^42^Ca). Total calcium and the stable calcium isotopes ^42^Ca and ^44^Ca will be analyzed using methods described elsewhere [31].

#### aBMD Measurement

Whole-body, right hip, and lumbar spine aBMD and whole-body fat mass and lean mass will be measured from a DXA scan (Lunar iDXA, GE Healthcare). Participants will be asked to remove excess jewelry and to wear shorts and a T-shirt. Scans will be performed on day 14 for the EUM group, day 21 for COCP users, and on the sole visit for LARC users.

#### Ultrasound

A nonradiating ultrasound technique (EchoLight, EchoLight S.p.a.) for measuring aBMD at the hip and lumbar spine will also be used in this study. The Royal Osteoporosis Society has recognized the technique as a clinical tool for measuring hip and spine aBMD, but there is no published research validating this technique in young, healthy adults. The site-specific aBMD readings from the ultrasound will be compared with those derived from DXA to validate the use of this equipment in future research. EchoLight ultrasound will be performed on day 14 for EUM, day 21 for COCP users, and the sole testing day for LARC users.

#### Bone Macro- and Microstructure

Bone microstructure, geometry, and volumetric density of the right tibia (distal 4% and 30% sites from the endplate) and radius will be assessed using HRpQCT (XtremeCT II, Scanco Medical AG). Trabecular and cortical volumetric bone mineral density and geometry, trabecular microarchitecture, cortical porosity, and estimated mechanical strength will be calculated for each scan. HRpQCT scans will take place on day 14 for the EUM group, day 21 for COCP users, and on the sole visit for LARC users.

#### Bone Material Properties

Reference point indentation will be performed on the flat surface of the medial tibial diaphysis using the handheld portable OsteoProbe (ActiveLife). The OsteoProbe is used to measure skeletal material mechanical properties by creating microindentations (150-260 μm depth) in the bone [32]. Reference point indentation will take place away from the main testing schedule for 1 day per month. The menstrual cycle phase and COCP status at the time of testing will be recorded.

#### Muscle and Tendon Characteristics

Measurements of muscle and tendon characteristics (see the *Muscle Strength*, *Functional Movement Testing*, and *Tissue Characteristics* sections) will be performed on every testing visit: days ~1, 7, 14, and 21 in the EUM group (equivalent to menses and midfollicular, ovulation, and midluteal phases), days 21 and 28 in the COCP group, and on the sole visit for the other HC groups.

#### Muscle Strength

Isometric and dynamic leg strength will be assessed using an isokinetic dynamometer (Biodex System 4 Pro, IPRS Mediquipe). For the isometric strength test, the participant will perform 2 submaximal warm-up reps of increasing effort followed by 3 maximal isometric contractions in extension, sustained for 5 seconds at 90° of knee flexion, with a 90-second rest period between each contraction. For the dynamic strength test, participants will complete 6 maximal repetitions in extension and flexion at 60°/s. Muscle endurance will be assessed by 15 maximal repetitions in extension and flexion at 180°/s. At least 3 minutes of rest will separate each test. Participants will be given verbal encouragement throughout the tests.

#### Functional Movement Testing

Participants will perform a single-leg drop to evaluate knee and ankle stability. From a raised platform, participants will stand on one leg with their arms crossed across their chest and “hop off” the platform, landing on the same leg. A total of 3 “hops” will be performed on each leg, with stability assessed using the qualitative assessment of single leg loading [33]. The frontal plane projection angle will be calculated by measuring the angle between the line from the proximal thigh to the midpoint of the knee joint and the line from the knee joint to the midpoint of the ankle, at the frame corresponding to maximum knee flexion [34].

#### Tissue Characteristics

Stiffness (N/m), tone (inferred from frequency; Hz), and elasticity (logarithmic decrement) of the *rectus femoris*, patellar tendon, *soleus*, *gastrocnemius*, and Achilles tendon will be measured in the rested state using digital palpation (MyotonPRO, Myoton AS). Participants will lie supine for the *rectus femoris* and patellar tendon measurements, and prone for the *soleus*, *gastrocnemius*, and Achilles tendon measurements using standardized protocols to ensure reliable recordings [35]. The MyotonPRO will be held perpendicular to the skin and 5 low-force (0.4 N) and short (15 ms) mechanical impulses applied, leading to oscillations of the underlying tissues from which stiffness, tone, and elasticity are derived. The MyotonPRO device records the CV between the 5 mechanical impulses within each set and displays this as a percentage next to each parameter. If any parameters are over a CV 3% threshold, the measurement will be repeated.

### Health and Lifestyle

#### Eating Attitudes Test 26-Items

The Eating Attitudes Test-26 item questionnaire will be completed at baseline and will be used for screening energy deficiency as a key risk factor for musculoskeletal health [36].

#### Habitual Calcium Intake

A food frequency questionnaire will be completed by participants on the final study visit to calculate habitual energy and calcium intake over the study period.

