## Methods

### Recruitment

Biochemical markers of bone and calcium metabolism and measures of musculoskeletal health and performance will be obtained in physically active women who are EUM (n=20) or HC users taking or administered COCP (n=20), implants (n=20), IUS (n=20), or hormonal injections (n=20). Participants will be aged 18-40 years; have stable body mass (defined as no change in self-reported body mass ≥5% over the previous 3 months); have a BMI between 18 and 30 kg/m^2^; have a regular menstrual cycle of 24-35 days in length; have not been taking any HC in the last 12 months (EUM group); have used the COCP for at least 12 months (COCP group); have used the IUS continuously for at least 2 years (IUS group); have used the implant continuously for at least 12 months (implant group); or have used the hormonal injection continuously for at least 2 years (injection group). Participants will be excluded if they have diagnosed premature ovarian insufficiency; are pregnant; are less than 2 years post partum; have given birth to more than 2 children; demonstrate evidence of disordered eating (defined as ≥20 on the Eating Attitudes Test-26 items) or have a self-reported eating disorder; report menstrual disturbance (amenorrhea or oligomenorrhea: <9 menstrual cycles in previous 12 months); are a habitual smoker (defined as ≥10 cigarettes per day); are taking any medication known to affect bone or calcium metabolism (eg, treatment for thyroid disorders); have a self-declared history of heart, liver or kidney disease, diabetes or thyroid disorder; self-report a bone injury in the previous 12 months; or have a total 25-hydroxyvitamin D (25(OH)D)<30 nmol/L at prescreening. Finally, any participants not in the injection group who report a history of using the hormonal injection will also be excluded from participation. We will aim to recruit matched sample sizes; however, some HC options are less common, and the study may be unable to achieve the desired sample size. Researchers have stated an end point for data collection of August 2024, giving 2.5 years of recruitment. If any group is underpowered, the sample achieved will be presented to mitigate influences from different time periods. An overview of the study schedule is illustrated in Figure 1; proposed biochemical markers of reproductive health and bone health are listed in Table 1.

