All continuous data will be checked for normality using a Shapiro-Wilk test and by visually checking for skewness and kurtosis. Markers of bone and calcium metabolism, reproductive function, and musculoskeletal health will be compared between contraceptive groups with a one-way between-group analysis of covariance (EUM [day 14] vs COCP [day 21] vs hormonal implant vs IUS vs hormonal injection groups) controlling for age, lean body mass (for bone measures only), physical activity, total 25(OH)D, and previous hormonal injection use. Categorical data from questionnaires will be analyzed using a chi-square test to test for differences between lifestyle, prior HC use, menstrual cycle history, and dietary choices between groups. Nonnormally distributed data will be tested using a Kruskal-Wallis test. Significant main effects of the group will be followed up with post hoc 2-tailed *t* tests with a Bonferroni correction (or Mann-Whitney *U* test for nonparametric data). Paired-sample 2-tailed *t* tests will be used to compare markers of bone and calcium metabolism, and reproductive and musculoskeletal function across the 2 time points in COCP users. Markers of bone and calcium metabolism, reproductive function, and muscle strength and tendon function will be compared between days in the menstrual cycle for the EUM group with a linear mixed effects model with the restricted maximum likelihood estimator to allow incorporation of incomplete data. Time will be the fixed effect (day 1 vs day 7 vs day 14 vs day 21), and a random intercept will be assigned to participants to account for the nonindependence of repeated measures. The significance of the fixed effects from each model will be determined with Sattherwaite degrees of freedom. The normality of the residuals for each model will be checked visually by plotting the residuals against the fitted values and from Q-Q plots. In the event of a significant main effect of time, pairwise comparisons with Holm-Bonferroni corrections and Kerward-Roger degrees of freedom will be used on the linear mixed effects model to identify differences between time points. A Bland-Altman plot will be used to assess the agreement between aBMD measured by ultrasound and DXA. Differences will be considered statistically significant at an α level of *P*<.05 with post hoc *P* values corrected for multiple comparisons.

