### Limitations

The cross-sectional study design prevents standardized and controlled administration (frequency and dose) of HCs in the COCP group, and the self-selection of hormonal contraception across groups may introduce selection bias. A randomized control trial design of HC interventions was not considered feasible for this research due to the length of time needed to elucidate meaningful effects, the impact on lifestyle and health care for participants, and the invasive procedures for the administration of LARCs. Functional movement—visually assessed from the location of the midpoint of the knee and ankle using video footage—may also be subject to observer bias; this bias will be minimized by using a single trained observer. Investigators will also be involved in the testing of all study participants and will not be blinded to HC groups.

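### Habitual calcium intake is collected but left out of the covariates for the between-group comparison of bone and calcium markers

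*Protocol article*

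**What the plan says.** Under Habitual Calcium Intake, the Protocol article plans: "A food frequency questionnaire will be completed by participants on the final study visit to calculate habitual energy and calcium intake".

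Under Statistical Analyses, the between-group model is set out: "Markers of bone and calcium metabolism, reproductive function, and musculoskeletal health will be compared between contraceptive groups", by one-way analysis of covariance, "controlling for age, lean body mass (for bone measures only), physical activity, total 25(OH)D, and previous hormonal injection use". The list is explicit, and neither calcium nor energy intake is on it.

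Diet appears once more in that section. Categorical questionnaire data go into a chi-square test "to test for differences between lifestyle, prior HC use, menstrual cycle history, and dietary choices between groups". No rule links the result of that test to adjustment of the outcome models.

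Under Limitations, the article concedes that "the self-selection of hormonal contraception across groups may introduce selection bias".

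**The concern.** The contraceptive groups are not randomised, so the covariate set is the main analytic protection for the between-group comparison. Eligibility (Recruitment) restricts body mass index, disordered eating, relevant medication and vitamin D status, but not calcium intake.

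The list already includes total 25(OH)D, a determinant of calcium metabolism that eligibility also restricts. Calcium intake is unrestricted, is collected, and has a plausible bearing on the same outcomes, yet it is left out.

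Two things are at stake. If intake is prognostic, precision is given away. If intake also differs between groups, part of a dietary difference would be read as a contraceptive effect. The Dissemination Policy says that the results are meant to inform prescribing.

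**Working it through.** **1. The plan's own figure.** Statistical Analyses gives 8 to 17 participants for the effect of time on calcium balance: 7 time points, eta squared 0.06-0.14, alpha 0.05, power 0.80. Take f² = η²/(1-η²), λ = N·m·f²/(1-ρ), and degrees of freedom m-1 and (N-1)(m-1). With m = 7 and ρ = 0.5 (an assumption; the article gives no ρ), the result is N = 17 at η² = 0.06 and N = 8 at η² = 0.14. The figure reproduces. It concerns change within eumenorrheic women only and has no bearing on the between-group covariates.

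**2. Precision.** The article gives no intake-outcome correlation r. Assume r = 0.2-0.5, after the other covariates.
- Fall in residual variance: r² = 0.04 to 0.25.
- Equivalent gain in sample size: 1/(1-r²) = 1/0.96 to 1/0.75 = 1.04 to 1.33, or 4-33%.

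**3. Bias if intake is imbalanced.** Bias in outcome SDs = standardised slope × intake difference in SDs.
- Slope 0.2-0.5, assumed difference 0.5 SD: 0.10 to 0.25 SD.
- Slope 0.1-0.3, assumed difference 0-0.8 SD: 0 to 0.24 SD.
- Difference 0: bias 0, whatever the slope.

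**4. What that bias does to a pairwise test.** With 20 women per group, the standard error is √(2/20) = 0.32 SD. The type I error of an uncorrected two-sided 5% test is Φ(b/0.316 - 1.96) + Φ(-b/0.316 - 1.96), where b is the bias in SDs.

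| Bias (SD) | Type I error |
|---|---|
| 0 | 5.0% |
| 0.15 | 7.6% |
| 0.24 | 11.8% |

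The plan uses an omnibus test followed by Bonferroni correction, so these figures show direction and rough scale, not the plan's actual error rate.

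**5. Cost of adding the covariate.** There are five groups of 20, so N = 100. With q covariates, residual degrees of freedom are 100 - 5 - q. For bone measures (five listed covariates) that is 90, or 89 with intake added. Take λ = N·f²/(1-R²), where R² is the share of residual variance that intake explains. The plan's eta squared range is borrowed here as an assumption, since the article states it for the time effect.

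| | η² = 0.06 | η² = 0.14 |
|---|---|---|
| Five covariates | 47.4% | 90.1% |
| Intake added, R² = 0 | 47.4% | 90.1% |
| Intake added, R² = 5-20% (assumed) | 49.7-57.7% | 91.6-95.8% |

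**6. The covariate it can replace.** Recruitment excludes any woman outside the injection group who has ever used the injection. Previous injection use, coded yes or no, is therefore absent in four groups and present in the fifth by definition, so it is aliased with group. A software routine would drop it, which leaves 91 effective residual degrees of freedom. Replacing it with intake gives 90, the number that the listed model implies.

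**The case against.** The strongest case against is that collecting a variable does not oblige anyone to adjust for it, and that extra or sensitivity models often sit in an analysis plan that is not shown. That would be decisive if the article were silent on adjustment. It is not: it states the covariate set for these outcomes, and that set can be judged as written.

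Several further objections stand and limit the point.

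- A reader might infer that intake is an established confounder here. The article does not support that. Confounding needs intake to differ by contraceptive group, and nothing shows that it does.
- A reader might infer that the study's sample size rests on the between-group comparison. Statistical Analyses does list a between-group null hypothesis, but the only number derived is for the within-cycle effect, where each woman is her own control and habitual diet largely cancels. The same holds for the paired tests in pill users.
- A reader might take intake to be a direct component of the calcium outcome. Background explains the urinary isotope ratio by bone uptake and release of calcium, and Biochemical Analyses measures it in first-void urine. Neither describes it as intake minus excretion. Fasted blood sampling may also dampen short-term dietary effects.
- Every magnitude above multiplies one assumption by another, and the largest bias is below one standard error of a 20-versus-20 comparison.

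A last objection is that intake is measured during contraceptive use, so adjustment could remove part of an effect that acts through diet. This is fair but does not defeat the change. Lean mass, physical activity and 25(OH)D are also measured during use, and the plan adjusts for them. Reporting both models lets the reader see the difference.

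**Conclusion.** The point holds as a weakness in the chosen covariate set, confined to the between-group analysis of covariance for bone and calcium markers. Intake is a plausible prognostic covariate and a possible confounder, and the chi-square comparison of dietary choices adjusts nothing. Whether any bias exists depends on an imbalance that the article neither shows nor rules out. The ranges for precision and bias hold only under the assumed correlations and the assumed 0.5 SD imbalance. The case for the change rests mainly on its low price: almost no power is lost even if intake explains nothing. Questionnaire error would make the adjustment incomplete, so it would reduce a dietary imbalance without being sure to remove it.

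**What to change.** In Statistical Analyses, add habitual calcium intake (mg/day from the food frequency questionnaire) as a covariate in the between-group models for the calcium isotope ratio, blood calcium, parathyroid hormone and bone turnover markers. Let it take the place of previous hormonal injection use. Report each of these comparisons with and without intake, fitted to the same women, and say that intake was measured during contraceptive use.

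The cost is at most one residual degree of freedom and no new data collection. A rule for missing questionnaires is needed. The questionnaire comes at the final visit, whereas the model uses day 14 for eumenorrheic women and day 21 for pill users, each before that group's last scheduled visit. A woman who leaves early could therefore have the outcome but no intake, and this can happen in those two groups but hardly in the single-visit groups. Imputation from the other covariates, stated in advance, would deal with it.

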### Statistical Analyses

The required sample size was calculated in G*Power 3 based on testing the null hypotheses: (1) there will be no change in calcium balance across the menstrual cycle; and (2) there will be no difference in calcium balance between the EUM group and HC users. There are no data examining calcium balance across the menstrual cycle. We anticipate a moderate to large effect size based on reported differences in calcium balance between women with low (anorexia nervosa patients) and normal estrogen (control participants; −50, SD 116 vs 77, SD 69 mg/day; *d*=2.27) [37], circulating blood calcium between the luteal and follicular phases (9.29, SD 0.52 vs 10.08, SD 0.48 mg/dL; *d*=1.08 [38]; and 2.1, SD 0.2 vs 2.3, SD 0.2 mg/dL; *d*=1.00 [39]), and urinary calcium excretion between the luteal and follicular phases (2.1, SD 1.5 vs 3.8, SD 2.2 μM/min; *d*=0.90) [40]. We estimate that between 8 and 17 participants are required to detect a significant main effect of time for calcium balance across the menstrual cycle (measured at 7 time points) with a moderate to large effect size (eta squared 0.06-0.14), an α of 0.05, and a 1– of 0.80.

All continuous data will be checked for normality using a Shapiro-Wilk test and by visually checking for skewness and kurtosis. Markers of bone and calcium metabolism, reproductive function, and musculoskeletal health will be compared between contraceptive groups with a one-way between-group analysis of covariance (EUM [day 14] vs COCP [day 21] vs hormonal implant vs IUS vs hormonal injection groups) controlling for age, lean body mass (for bone measures only), physical activity, total 25(OH)D, and previous hormonal injection use. Categorical data from questionnaires will be analyzed using a chi-square test to test for differences between lifestyle, prior HC use, menstrual cycle history, and dietary choices between groups. Nonnormally distributed data will be tested using a Kruskal-Wallis test. Significant main effects of the group will be followed up with post hoc 2-tailed *t* tests with a Bonferroni correction (or Mann-Whitney *U* test for nonparametric data). Paired-sample 2-tailed *t* tests will be used to compare markers of bone and calcium metabolism, and reproductive and musculoskeletal function across the 2 time points in COCP users. Markers of bone and calcium metabolism, reproductive function, and muscle strength and tendon function will be compared between days in the menstrual cycle for the EUM group with a linear mixed effects model with the restricted maximum likelihood estimator to allow incorporation of incomplete data. Time will be the fixed effect (day 1 vs day 7 vs day 14 vs day 21), and a random intercept will be assigned to participants to account for the nonindependence of repeated measures. The significance of the fixed effects from each model will be determined with Sattherwaite degrees of freedom. The normality of the residuals for each model will be checked visually by plotting the residuals against the fitted values and from Q-Q plots. In the event of a significant main effect of time, pairwise comparisons with Holm-Bonferroni corrections and Kerward-Roger degrees of freedom will be used on the linear mixed effects model to identify differences between time points. A Bland-Altman plot will be used to assess the agreement between aBMD measured by ultrasound and DXA. Differences will be considered statistically significant at an α level of *P*<.05 with post hoc *P* values corrected for multiple comparisons.

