### Aims and Hypotheses

There is limited evidence for the overarching effects of estrogen on bone and calcium metabolism and musculoskeletal performance and even fewer studies investigating the impact from chronic use of HCs. Our primary aims are to (1) investigate the effect of menstrual cycle phase on bone and calcium metabolism, and musculoskeletal health and performance in EUM, non-HC users (EUM group); and (2) investigate the effects of HC use on bone and calcium metabolism, and musculoskeletal health and function. Our secondary aims are to (1) determine the validity of an ultrasound-based method of measuring hip and spine aBMD compared with “gold standard” DXA and (2) compare calcium and bone metabolism, reproductive hormones, and musculoskeletal function between the pill phase and non-pill phase of COCP use.

This study will test the following hypotheses in 2 study designs. Menstrual cycle phase (within-groups design): (1) calcium and bone metabolism is decreased during the ovulatory phase compared with other phases; and (2) muscle strength and tissue mechanical properties differ across the menstrual cycle. HC use (between-groups design): (1) calcium and bone metabolism is higher in the implant and injection groups compared with IUS (which exerts localized effects) and EUM (ovulatory phase) groups, and lower in the COCP group; (2) estradiol and progesterone are lower in HC users compared with the EUM group during the ovulatory phase; (3) bone macro- and microstructure, muscle strength, and tissue properties are different in HC users compared with the EUM group; and (4) calcium and bone metabolism, reproductive hormones, and musculoskeletal function are different between the pill phase and non-pill phase of COCP use.

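### The five-group ANCOVA adjusts for previous hormonal injection use, which the eligibility rules fix at zero in four groups, so the covariate is wholly or partly aliased with injection-group membership

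*Protocol article*

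**What the plan says.** All references are to the protocol article.

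- **Statistical Analyses** specifies a one-way between-group ANCOVA with one level for each of the five contraceptive groups. The adjustment set is given as "controlling for age, lean body mass (for bone measures only), physical activity, total 25(OH)D, and previous hormonal injection use". Post hoc tests with a Bonferroni correction follow only if the main effect of group is significant. For data that are not normal: "Nonnormally distributed data will be tested using a Kruskal-Wallis test".
- **Recruitment** states that "any participants not in the injection group who report a history of using the hormonal injection will also be excluded from participation". Entry to the injection group itself is defined by the phrase "have used the hormonal injection continuously for at least 2 years (injection group". The target is 20 per group.
- **Aims and Hypotheses** predicts that "calcium and bone metabolism is higher in the implant and injection groups compared with IUS". The same direction is predicted against EUM women, and the opposite direction for COCP users.

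The article does not say how previous injection use will be coded.

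**The concern.** A covariate helps a group comparison when it varies within groups and may be unevenly spread between them. This one is zero for every EUM, COCP, implant and IUS participant, and can be non-zero only among injection users. Its slope can therefore be estimated only within the injection group, and it can alter only contrasts that involve that group. Between groups, a difference in injection history is the exposure under study.

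At stake is the adjusted comparison of the injection group with IUS and EUM, which one of the between-group hypotheses needs. The ANCOVA is the planned method for bone and calcium markers, reproductive function and musculoskeletal health, so the covariate enters most between-group analyses.

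**Working it through.** **The plan's own figure.** The only computed sample size is 8 to 17 participants for the effect of time across the menstrual cycle. It reproduces exactly (eta squared 0.14 gives 8, 0.06 gives 17; 7 time points, within-person correlation assumed 0.5, sphericity assumed). It does not involve this covariate. The article gives no power figure for the between-group test, so the effect sizes below are assumptions.

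**Inputs.** From the article: five groups of 20, α = 0.05, and the covariates age, physical activity and total 25(OH)D (lean mass is added for bone measures only and is left out here). Assumed: the three other covariates are random draws unrelated to outcome, the residual SD is 1, and the group test is adjusted for all covariates (Type III).

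**Step 1: rank.** The design has an intercept, 4 group indicators, the injection covariate and 3 other covariates: 1 + 4 + 1 + 3 = 9 columns. If any use counts, including current use, the covariate is 1 for all 20 injection users and 0 for the other 80, which is the injection indicator. The rank is 8 of 9. The adjusted group test has 3 df instead of 4, and injection minus EUM is not estimable.

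**Step 2: noncentrality, injection group alone raised by 1 SD.** Ignoring chance imbalance in the other covariates, λ = n Σ(μ_j − μ̄)².
- Without the covariate: λ = 20 × (1 − 5 × 0.2²) = 20 × 0.8 = 16. In the simulated layout λ = 15.67, and with 4 and 92 df the power is 0.89.
- Any-use coding: only the other four group means enter and they are equal, so λ = 0 and power equals α, 0.05, whatever the size of the injection effect.

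**Step 3: an earlier separate spell in k of the 20 injection users.** The model is now full rank. The injection mean at covariate zero rests on the 20 − k users without a spell, so the SE of injection minus EUM is about √(1/20 + 1/(20 − k)). For k = 2 this is 0.32 and for k = 18 it is 0.74. The layout values, which include chance imbalance, are slightly larger.

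| Coding (injection-only shift of 1 SD) | Group df | Power | SE, injection − EUM |
|---|---|---|---|
| Covariate omitted, or zero for everyone | 4 | 0.89 | 0.33 |
| Any use, including current | 3 | 0.05 | not estimable |
| Earlier spell in 2 of 20 | 4 | 0.86 | 0.34 |
| Earlier spell in 5 of 20 | 4 | 0.78 | 0.36 |
| Earlier spell in 10 of 20 | 4 | 0.60 | 0.41 |
| Earlier spell in 15 of 20 | 4 | 0.35 | 0.51 |
| Earlier spell in 18 of 20 | 4 | 0.16 | 0.76 |
| Years of use, assumed 2 to 10 | 4 | 0.21 | 0.64 |
| Years of use, assumed 2 to 6 | 4 | 0.14 | 0.81 |

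In the last two rows the contrast is also an extrapolation to zero years of use, which no injection user has.

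**Step 4: a pattern like the stated hypothesis.** Take implant and injection +0.5 SD, COCP −0.5 SD, EUM and IUS 0, with any-use coding as the worst case.
- Without the covariate: Σμ² = 0.75 and μ̄ = 0.1, so λ = 20 × (0.75 − 5 × 0.01) = 14. Power in the layout is 0.84.
- With it: the remaining four groups have Σμ² = 0.5 and mean 0, so λ = 20 × 0.5 = 10. Power in the layout is 0.73.
- At 1 SD, power is above 0.99 both ways.

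**The case against.** The strongest reply is that the damaging result needs a particular coding. Injection users are defined by their current method, so previous use can naturally be read as use before the current spell. If none had such a spell, the covariate is constant, drops out and does no harm. Even with any-use coding, software may drop the redundant covariate instead of a group term, which returns the ordinary 4-df test. The post hoc t tests are not stated to be covariate-adjusted, so plain t tests would still estimate the injection contrasts once the omnibus test is significant. All of this stands, and it limits the size of the problem. It does not give the covariate a useful role under any coding.

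A reader might go further in three ways that the documents do not support:

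- *That the injection effect is always removed from the group test.* This needs both any-use coding and a covariate-adjusted test, and the article states neither.
- *That the omnibus test collapses from 0.89 to 0.05 in this trial.* Those figures apply when the injection group alone differs. The article also predicts differences for the implant and COCP groups, and under that pattern the loss is small (Step 4).
- *That only the injection group's adjusted mean moves.* Adjusted means are evaluated at the overall covariate mean, so all five shift when the model is full rank. What changes is the set of contrasts that involve the injection group.

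**Conclusion.** The two sections do not fit together, and the covariate is wrong as written. It is structurally zero in four groups, so its effect ranges from none to making the adjusted injection contrast inestimable. For an assumed injection-only shift of 1 SD, power is 0.89 without it. With it, power is 0.05 under any-use coding and 0.86 to 0.16 if 2 to 18 of 20 users had an earlier spell, with no loss if none had. These values rest on 20 per group, a covariate-adjusted group test and effect sizes that the article does not supply.

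The harm falls mainly on the adjusted injection contrasts. Contrasts among the other four groups, the Kruskal-Wallis route, the within-cycle mixed model, the COCP paired tests and the ultrasound-DXA agreement analysis are not affected.

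**What to change.** Delete previous hormonal injection use from the covariates of the between-group ANCOVA. The exclusion rule already controls it by design in the four other groups. If duration of use or earlier spells are of interest, examine them within the injection group only, as a separate descriptive or regression analysis, and define the variable there.

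The cost is one phrase. No participants, measurements or visits change, and under none of the codings above is the between-group test worse without the covariate. The change should be made before the between-group data are analysed, so that the coding is not left open until results can be seen.
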